## Abstract

**Background:**

Obesity prevention is a major public health priority. Despite the health risks associated with weight gain, there has been a distinct lack of research into effective interventions to prevent, rather than treat, obesity particularly at high risk life stages such as menopause in women. This paper describes the rationale for and design of a 2-year randomized controlled trial (RCT) (the 40-Something Study) aimed at testing the feasibility and efficacy of a relatively low intensity intervention designed to achieve weight control in non-obese women about to enter the menopause transition.

**Methods and design:**

The study is a parallel-group RCT consisting of 12 months of intervention (Phase 1) and 12 months of monitoring (Phase 2). Non-obese pre-menopausal healthy females 44–50 years of age were screened, stratified according to Body Mass Index (BMI) category (18.5-24.9 and 25–29.9 kg/m^2^) and randomly assigned to one of two groups: motivational interviewing (MI) intervention (n = 28), or a self-directed intervention (SDI) (control) (n = 26). The MI intervention consisted of five consultations with health professionals (four with a Dietitian and one with an Exercise Physiologist) who applied components of MI counselling to consultations with the women over a 12 month period. The SDI was developed as a control and these participants received print materials only. Outcome measures were collected at baseline, three, 12, 18 and 24 months and included weight (primary outcome), waist circumference, body composition, blood pressure, plasma markers of metabolic syndrome risk, dietary intake, physical activity and quality of life. Analysis of covariance will be used to investigate outcomes according to intervention type and duration (comparing baseline, 12 and 24 months).

**Discussion:**

The 40-Something study is the first RCT aimed at preventing menopausal weight gain in Australian women. Importantly, this paper describes the methods used to evaluate whether a relatively low intensity, health professional led intervention will achieve better weight control in pre-menopausal women than a self-directed intervention. The results will add to the scant body of literature on obesity prevention methods at an under-researched high-risk life stage, and inform the development of population-based interventions.

**Trial registration:**

ACTRN12611000064909

## Background

Obesity prevention in adults has the potential to significantly decrease the burden of disease in the population and costs to the health system [1,2]. Prevention of weight gain is particularly important at life stages where fat is deposited abdominally, since this confers additional health risks by contributing to metabolic syndrome [3,4]. Longitudinal studies have shown that middle age (45–54 y) is a high risk stage for weight gain in Western Women [5-8]. Prior to the onset of menopause, women have a low prevalence of cardiovascular disease and associated risk factors [9]. The physiological change initiated by menopause alters this level of risk, primarily through the preferential deposition of fat abdominally due to oestrogen deficiency [5,10-12]. National data show the prevalence of abdominal overweight and obesity in Australian women jumps from 66.8% in the 45–54 year age group to 77.9% in the 55–64 year age group [13], with the latter group having a dramatically higher increase in cardiovascular disease [14]. An estimated 48% of coronary events in women are attributable to metabolic syndrome [15]. Weight gain after menopause also increases the risk of breast cancer [16].

While there is a substantial body of evidence showing that weight loss in the obese reduces cardiovascular risk, the body of evidence on weight gain prevention interventions is scant [17], with only one RCT investigating whether weight gain prevention in pre-menopausal women can mitigate the increase in cardiovascular risk usually associated with menopause [18,19]. The Women’s Healthy Lifestyle Project conducted in the United States was designed to prevent weight gain and increased cardiovascular risk associated with menopause [18,19]. Pre-menopausal women (44–50 y, N = 535) randomized into a lifestyle intervention group (15-session diet and exercise education program followed by a maintenance program) lost on average 0.1 (5.2) kg after 54 months compared with a gain of 2.4 (4.9) kg in the assessment-only group [19]. While the trial showed that it was possible to prevent menopausal weight gain and to limit the typical post-menopausal rise in low density lipoprotein (LDL) cholesterol, the researchers acknowledged that the 15-session intervention held over 20 weeks was labour intensive and required a substantial time commitment from participants [20]. There is a need for the development of less intensive interventions that could feasibly be implemented on a population basis.

While women are known to attempt weight control (defined as weight maintenance for those of healthy weight and weight loss for the overweight) [21], self-directed efforts have not prevented population weight gain. Data from over 12,000 mid-age women in the population-wide Australian Longitudinal Study on Women’s Health showed 70% of participants reported behaviours aimed at losing weight or preventing weight gain, but they were mostly unsuccessful [21]. In the first two years of the study, the women without surgical menopause gained a mean (SD) of 1.04 (4.7) kg [22], and the cohort continued to gain weight at 0.5 kg/year over the next three years [23]. In a study of the weight control practices used by the women [21] the only group who managed to successfully prevent weight gain included a commercial program in addition to the typical public health strategies of 'cutting down on the size of meals and snacks plus cutting down on fats and sugars plus exercise’. This demonstrates the need for population based interventions that provide the face-to-face support typical of commercial programs, in addition to the more traditional awareness raising and education strategies.

In Australia, a model utilising face-to-face health practitioner support with potential to be implemented nationally already exists within the healthcare system but has not been used with this target group. The Chronic Disease Management scheme of Medicare Australia funds five consultations with allied health professionals in a 12 month period for those referred by a primary care physician with chronic conditions and complex medical problems [24]. This program could potentially be extended to women on the cusp of menopause, given it provides face-to-face contact but is still relatively low intensity. The addition of MI as a client-centred counselling technique to the health professional consultations provides the opportunity to strengthen commitment to behaviour change by reducing resistance to change and enhancing intrinsic motivation [25] with evidence of improved quality of nutrition and physical activity counselling [26]. The efficacy of this model in preventing weight gain in pre-menopausal women needs to be tested. In fact, no interventions to prevent menopausal weight gain have been tested in Australian women to date.

### Study aim

This paper describes the research protocol for an RCT (the 40-Something Study) aimed at testing the feasibility and effectiveness of applying a health professional led, weight gain prevention intervention in non-obese women about to enter the menopause transition (aged 44–50 years). The feasibility of recruiting to the study, ability to retain participants and the suitability of the written materials were tested along with the preliminary effectiveness of the intervention. There are two hypotheses:

1. Women in the MI group will lose at least 2.5 kg by the end of the intervention (12 months post-baseline) and maintain that loss for a further 12 months (to 24 months post-baseline).

2. Women in the SDI (control) will gain 0.5 kg by 12 months and 1.0 kg by 24 months.

## Methods/design

### Study design

The study design is a parallel-group RCT as shown in Figure 1. Weight change outcomes for the intervention provided by health professionals utilising MI will be compared with equivalent advice provided in written format (SDI). At the conclusion of the 12-month intervention (Phase 1), goals will be reassessed and participants entered into a 12-month monitoring phase (Phase 2) to determine whether intervention effects can be sustained. The University of Newcastle’s Human Ethics Research Committee approved this study (approval number H-2010-0030). Written informed consent was obtained from all participants prior to enrolment. The RCT was designed to adhere to the Consolidated Standards of Reporting Trials (CONSORT) guidelines [27,28] and the trial protocol was registered with ACTRN12611000064909. Following eligibility screening (using criteria shown in Table 1), weight and height were measured by researchers to calculate BMI, with participants categorised as Healthy weight: 18.5 to 24.9 kg/m^2^ or Overweight: 25–29.9 kg/m^2^. Equal numbers of women in each BMI category were then randomised to the MI or the SDI.

**Figure 1 F1:**
[figure not shown]
**CONSORT Flow chart describing the progress of participants through the trial**[28]**.**

**Table 1 T1:** Eligibility criteria for the 40-something study

** *Inclusion criteria* **	** *Exclusion criteria* **
Female	Hysterectomy and or oophorectomy
BMI between 18.5 and 30 kg/m^2^	Pregnant
Menstrual period within preceding 3 months	Taking hormone replacement therapy
Born in the years 1960 to 1966	Reported diagnosis of cardiovascular disease, diabetes, cancer
Able to attend appointments at the University	
Able to communicate in English	

### Participants and recruitment

Non-obese (BMI between 18.5 and 30 kg/m^2^) pre-menopausal women aged 44–50 years were recruited from the region surrounding Newcastle, NSW, Australia between May and July of 2010. Recruitment channels included radio and television interviews, newspaper articles and flyers placed in medical clinics, and University notice boards. Women expressing interest in the study contacted researchers and were screened for eligibility over the telephone by the first two authors according to a documented protocol based on the inclusion and exclusion criteria shown in Table 1. Weight and height were self-reported by the women and BMI calculated. Due to the limitation of self-reported height and weight, the BMI criterion was re-checked using laboratory measurements at the first assessment visit, and anyone who had misreported or underestimated their weight to the extent that their BMI was in the obese range was subsequently excluded. One woman was found to be obese (BMI over 30 kg/m^2^) at this stage. Participants not meeting all of the eligibility criteria during telephone and laboratory screening were excluded for the reasons shown in Figure 1.

### Randomization, blinding and quality assurance

Randomization was achieved using a computer-based random number sequence. Once written consent was obtained, participants were enrolled in the study. Baseline assessments were then completed and BMI status was checked and the women were categorised as healthy weight or overweight. At the end of the first assessment the enrolled women were given a participant identification number by a researcher ([name]). The numbers used were from a random allocation sequence generated by a statistician using a computer-based random number-producing algorithm to ensure an equal chance of allocation to each intervention group (the Plan procedure (Proc Plan) in the SAS statistical software package) in block lengths of six. The sequence was divided into two separate lists — one for each BMI category. [name] checked the BMI category of each participant at the conclusion of the first assessment, then allocated the participant to the next vacant number sequence on either the healthy weight list or the overweight list as appropriate. This ensured approximately equal numbers of healthy weight and overweight women were assigned to each intervention group. [name] remained blinded to group assignment. A separate version of each list, with intervention group appearing next to each identification number was only given to one researcher ([name]) who was unable to remain blinded after baseline measures since she delivered the face-to-face Dietitian consultations. She phoned the women within a day of their baseline measures to inform them of their group assignment.

All other researchers and research assistants remained blinded to group assignment throughout the study. When presenting for subsequent assessments, participants were reminded not to reveal their assignment group to the researchers and research assistants. To minimise the effects of the potential bias of [name] being unblinded, this researcher only assisted with automated measures at 3 months. However, at 12 and 24 months [name] was required to collect waist circumference measures for measurement consistency with the baseline collection of that measure. To confirm success of researcher blinding an audit tool was constructed and administered at the end of each measurement session. All assessors recorded which group they believed the participants were assigned to (MI or SDI), and indicated the reason for their answer from a list of tick box items, which included a) just a guess, b) participant revealed it to me directly, c) participant revealed it to me indirectly, d) based on the participant results, or e) other reason, with space provided to record the 'other’ answer. The project was monitored by a Research Management Committee who met monthly to oversee the implementation of the project.

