### Protocol

#### **
*Phase 1: Intervention delivery 0 to 12 months*
**

In phase 1 the women completed baseline assessments, were assigned to groups to receive the relevant intervention, were reassessed at 3 months for compliance to protocols, and a final assessment was conducted at 12 months. The intervention components are shown in Additional file 2.

1) MI group – five x 60 minute Health Professional consultations.

Within a month of baseline measures being taken, women in this group received a 1 hour consultation with a Dietitian (consultation 1), followed by a one hour consultation with an Exercise Physiologist (consultation 2) around the same time. They received three subsequent one hour appointments with the same Dietitian three, six and nine months later (consultations 3, 4 and 5). Each consultation followed a protocol incorporating individualised counselling, tailored according to assessment results, and was delivered using the principles of MI. The health professionals (Accredited Practising Dietitian and Exercise Physiologists) were registered Medicare Australia providers trained to promote changes in behaviour in order to achieve weight maintenance or weight loss goals. They had also undertaken additional training in the application of MI. The same Accredited Practising Dietitian ([name]) conducted all Dietitian appointments, and the Exercise Physiology consultations were shared between two practitioners. While attending consultations 1 and 3 the women were given print copies of their assessment results (biochemistry, anthropometry, diet and physical activity analysis) from baseline and 3 month measures respectively and received intervention support materials (weight control pamphlet relevant to their baseline BMI, a weight tracking sheet, menstrual record sheet, and a food and physical activity diary for self-monitoring) at consultation 1. Weight control goals and behaviour change strategies (three for diet and three for physical activity) were negotiated in writing during consultations.

2) SDI group (control) – written advice only

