### Outcome measures

Outcome measures were assessed for all participants at baseline, between May-September 2010, and reassessed at 3, 12, 18 and 24 months (end of monitoring phase 2) as shown in Additional file 3. The primary endpoints are at 12 months to determine the effects of the intervention and at 24 months to assess whether the intervention effects were maintained. Weight was the primary outcome measure.

#### **
*Measurement procedure*
**

Assessments were conducted in the early morning, in the anthropometry laboratory at the University of Newcastle (Australia). Procedures and protocols for the measurements were standardised, documented, and research assistants were trained in their application prior to collection. Participants fasted overnight, and upon entry to the laboratory removed their shoes and excess clothing. The assessment process lasted approximately 60 minutes for each participant, and they were provided with breakfast prior to leaving the laboratory.

#### **
*Anthropometry*
**

Height was measured using a stadiometer (Surgical and Medical Products) correct to 0.1 cm using the stretch stature method. Weight and body composition (percentage fat, skeletal muscle mass) were measured at all time points using BIA Omron HBR-500 Body Composition Monitor with Scales correct to 0.1 kg. BMI was calculated using the standard equation (weight [kg]/height[m]^2^). Waist circumference was collected as a valid marker of central adiposity [44] using a non-extensible steel tape to measure at the level of the mid-point between the lower costal border and the iliac crest (KDS F10-02, KDS Corporation, Osaka, Japan). Two measures were collected and averaged. Visceral adipose tissue area was estimated using the InBody720 Body Composition Analyzer (Biospace) at 12, 18 and 24 months.

#### **
*Biomarkers of metabolic syndrome*
**

Thirty millilitres of blood was collected from each participant by a trained phlebotomist and analysed by a laboratory accredited with the National Association of Testing Authorities Australia. Fasting measures of total cholesterol, low density lipoprotein cholesterol, high density lipoprotein cholesterol, triglycerides and glucose were assessed. Blood samples have been stored in a -80°C freezer for further analyses (sex hormones, insulin, leptin, and antioxidants to validate dietary intake) should funds become available.

#### **
*Blood pressure and resting heart rate*
**

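### Waist circumference, a secondary outcome taken by hand, is measured at 12 and 24 months by the unblinded dietitian who counsels the MI arm, so its between-arm comparison is open to assessor bias

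*Protocol article*

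**What the plan says.** All references are to the protocol article.

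**Who knows the allocation.** Under Randomization, blinding and quality assurance: "A separate version of each list, with intervention group appearing next to each identification number was only given to one researcher", a person "who was unable to remain blinded after baseline measures since she delivered the face-to-face Dietitian consultations". Under Protocol (Phase 1), a single Accredited Practising Dietitian "conducted all Dietitian appointments, and the Exercise Physiology consultations were shared between two practitioners". Each MI woman therefore has four one-hour sessions with her (consultations 1, 3, 4 and 5). SDI women have none.

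**What she may measure.** The blinding section recognises that her knowledge of group could bias measurement, and as a safeguard "this researcher only assisted with automated measures at 3 months". It then makes an exception for 12 and 24 months, when she "was required to collect waist circumference measures for measurement consistency with the baseline collection of that measure". Everyone else on the research team is said to have stayed blinded. Assessors also record which group they think each woman is in.

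**What waist is.** Under Outcome measures: "Waist circumference was collected as a valid marker of central adiposity", "using a non-extensible steel tape to measure at the level of the mid-point between the lower costal border and the iliac crest". Two readings are averaged. Weight, the primary outcome, comes from an electronic body composition monitor with scales.

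**When it counts.** "The primary endpoints are at 12 months to determine the effects of the intervention and at 24 months to assess" whether effects were maintained.

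**The concern.** Finding the mid-point and setting the tape tension both call for judgement. The person making that judgement at the two endpoint visits knows the arm and has counselled one arm only. The article treats her unblinding as a risk at 3 months, then lifts the restriction for a hand-taken measure at the visits where the effect is to be judged.

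What is at stake is the credibility of the waist result. Waist is the first outcome the abstract lists after weight, and abdominal fat gain at menopause is central to the trial's rationale in the Background. If a waist difference is reported at 12 or 24 months, a reader cannot tell a treatment effect from a difference in how the tape was read.

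**Working it through.** **1. Same person?** Names are removed from the text. The blinding section describes one unblinded researcher, states the 3-month restriction on her, and goes straight on to the 12- and 24-month exception. Read together, these sentences describe one person, and her stated role is delivering the Dietitian consultations.

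**2. Does the consistency reason hold?** Write the observed between-arm difference at follow-up as

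observed = true effect + (m − m) + (b_MI − b_SDI),

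where m is the measurer's own offset, the same for every woman she measures, and b is any reading error that depends on knowing the arm. The m terms cancel whoever holds the tape, provided measurers are not assigned by arm. The b terms cancel only if the measurer does not know the arm. Keeping the baseline measurer therefore protects against an error that already drops out and admits one that does not. Averaging two readings does not help, because the same person takes both.

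**3. Was the measurer kept constant anyway?** The abstract lists waist among the outcomes collected at baseline, 3, 12, 18 and 24 months, and Outcome measures gives the same visits for outcomes in general. At 3 months this researcher did only automated measures. If waist was taken then, someone else took it. That is a fair inference, but no sentence states it.

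**4. Does any safeguard cover it?** The audit of assessors' guesses tests whether blinded staff stayed blinded. It can neither detect nor correct bias in a person who holds the allocation. The limitations in the Discussion mention efforts at researcher blinding but not this exception.

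**5. Size (illustration only).** The article gives no waist figure to reproduce. Inputs:
- n = 22 per arm, the required number in Sample size before the attrition allowance
- SD of waist change 4, 5 or 6 cm (assumed)
- arm-dependent reading error e = b_MI − b_SDI of 0.5, 1 or 2 cm (assumed)
- no true effect, normal approximation, two-sided 5% test

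Standard error = SD × √(2/22). This gives 1.21, 1.51 and 1.81 cm for SD 4, 5 and 6.

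Type I error = Φ(d − 1.96) + Φ(−d − 1.96), with d = e / standard error.

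For SD 5 and e = 1: d = 1/1.51 = 0.66, so the type I error is 0.102.

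| Reading error | SD 4 cm | SD 5 cm | SD 6 cm |
|---|---|---|---|
| 0.5 cm | 7.0% | 6.3% | 5.9% |
| 1 cm | 13.2% | 10.2% | 8.6% |
| 2 cm | 38.2% | 26.4% | 19.8% |

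**The case against.** The best defence is that this is an open trade-off on a secondary outcome. The article names the risk, limits it in part, states the exception and gives a reason. Procedures are standardised and documented. Sample size and the primary test rest on weight, and the Discussion concedes that secondary outcomes are underpowered. Visceral fat area from a body composition analyser is also compared between groups at 12 and 24 months, so waist is not the only abdominal-fat outcome. All of this stands, and it limits the weight of the point. It does not remove the bias: disclosure leaves the readings as they are, and the visceral fat measure has no baseline value to adjust for.

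A reader might infer more than the article supports:

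- *That the primary result is compromised.* It is not, through this route: weight is scale-read.
- *That a blinded assessor certainly took waist at 3 months.* The assessment schedule is in an additional file that is not shown, and the Anthropometry text gives no time points for waist.
- *That she knew upcoming allocations while measuring later women at baseline.* The article says she was unblinded after baseline measures. It does not say when she received the list, and a different, blinded researcher assigned each woman the next number. The inference is unproven.
- *That the bias favours MI, or that the type I error is 10%.* Nothing in the article fixes a direction, and any single percentage depends on the SD and reading error assumed.

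**Conclusion.** The point holds as a weakness in outcome assessment for one secondary outcome. At 12 and 24 months, tape-measured waist is taken by an assessor who knows the arm and has counselled one of the two, and the reason given does not outweigh that. This rests on the text alone.

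The size of the bias is unknown. Under the assumptions above, the two-sided type I error for waist would rise from 5% to about 6-7%, 9-13% or 20-38% for a reading error of 0.5, 1 or 2 cm. Those ranges show how sensitive the comparison is; they do not estimate what happened. The arrangement should be changed or, if it is too late, plainly reported.

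**What to change.** Have a blinded research assistant, trained in the standardised procedure, take waist at 12 and 24 months, and keep the dietitian on automated measures. The article already describes blinded, trained research assistants, so the change should be cheap, although it does not say which of them are trained in the waist measure. The statistical cost is some added inter-measurer noise, common to both arms. It lowers precision slightly and does not bias the comparison.

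Where readings are already taken, which the article's 2010-2013 timeline makes likely for at least 12 months:

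- Keep the 12- and 24-month waist comparison, because those visits answer the trial's questions about effect and maintenance.
- Label it as assessed by an unblinded measurer wherever it is reported.
- Name the exception in the limitations.
- If waist readings by a blinded assessor exist at 3 or 18 months, show them as supportive only. Making them the main comparison would change the question, since 3 months falls partway through the intervention.

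The reporting changes cost a few sentences.
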